**Methods:**

A pilot and national trial will measure implementation feasibility, acceptability, and effects of the MPACT intervention on treatment practice change, clinic culture, patient retention, and patient posttraumatic stress symptoms (PTSS). The pilot will be a single-arm 5.5-month pilot study of MPACT conducted in 2 Arizona methadone treatment clinics (rural and urban) among 100 patients and 22 staff. The national trial will be a 20-month cluster randomized trial conducted among 30 clinics, 600 patients (20 per clinic), and 480 staff (18 per clinic). Data will be gathered by staff and patient surveys and patient chart review. The primary study outcome is increased patient methadone treatment retention measured as (1) time to first treatment interruption from study enrollment; (2) active in treatment at enrollment, day 30, 60, 90, and 120; and (3) continuous days in treatment during the study period. Secondary study outcomes include reductions in vicarious trauma and PTSS among enrolled opioid treatment program staff and PTSS among enrolled patients.

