**Figure 1 figure1:**
[figure not shown]
Potential inner setting factors impacting methadone treatment outcomes.

To this end, we developed Methadone Patient Access to Collaborative Treatment (MPACT): a multimodal intervention to increase staff awareness of and readiness to adopt MMT treatment innovation. MPACT promotes treatment flexibilities allowed by federal regulators and patient-centered, trauma-informed MMT and seeks to empower OTP staff and clinic groups to adopt these treatment flexibilities by addressing staff VT and PTSS, which will improve treatment quality and ultimately MMT retention. The objective of this study is to test the adoption, feasibility, and impact of MPACT on methadone treatment delivery and patient outcomes. There are 6 specific aims for the MPACT study over the 6-year project period. The specific aims are listed here and will be described in the following subsections.

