### Measures

The primary study outcome is increased patient methadone treatment retention. This outcome is measured in three ways: (1) time to first treatment interruption, calculated as the number of days to first missed dose from day 0 (MPACT enrollment); (2) evidence of being active in treatment, a binary (yes or no) if receiving dose at points in time on day 0, 30, 60, 90, and 120; and (3) continuous days in treatment during the study period, calculated as time (days) to discharge. Data measuring this outcome are gathered by patient surveys and chart reviews.

Secondary study outcomes include reductions in VT and PTSS among enrolled clinic staff and PTSS among enrolled patients. Data measuring secondary outcomes are gathered by a survey of staff and patients enrolled in the study. For staff and patients, PTSS are measured using the 8-item posttraumatic stress disorder symptoms screener otherwise known as the PCL-5 [35]. Staff VT is measured by the Vicarious Trauma Scale [37], burnout is measured by a 3-item scale [45], and compassion satisfaction and compassion fatigue are measured by the shortened, 9-item Professional Quality of Life Scale for staff [46].

The degree to which methadone treatment is patient-centered is also a secondary outcome measured through staff surveys (assessing whether they believe they are providing it) and patient surveys (assessing whether they feel they are experiencing it). Patient-centered care competency is measured by a 19-item scale [47] including the following subscales: respecting patient perspectives, promoting patient involvement in the care process, providing patient support, and advocating for patients. Patient-centered care, as defined by the study team, is measured using a 5-item instrument that reflects the concepts of patient-centered care introduced during the accredited training modules. This scale is administered to staff, with an adapted version used for patients.

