### Data Collection

Primary and secondary study outcomes will be measured by surveys and patient chart reviews. Surveys will be administered monthly for the pilot study: assessment 1 (baseline at enrollment) and assessment 2-5 in 30-day sequences through the study period, with a contact reminder at day 27 and a completion forgiveness period of 5 days (day 35). Table 1 displays the sequencing of measures across the 5 pilot surveys.

**Table 1 table1:** Sequencing of Methadone Patient Access to Collaborative Treatment (MPACT) primary and secondary measures (assessment 1-5).

Construct		Assessment 1 (enrollment)			Assessment 2		Assessment 3		Assessment 4		Assessment 5 (study conclusion)
		Staff items, n	Patient items, n								

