**Implementation**											
	MPACT feasibility, accept and fit; likelihood of continuing practices	5	—	—		—		—		✓	

^a^Not applicable.

^b^SUD: substance use disorder.

^c^MMT: methadone maintenance treatment.

^d^OD: opioid overdose.

^e^LEC: Life Events Checklist.

^f^PCL-5: Posttraumatic Stress Disorder Checklist.

^g^Patients only.

^h^ProQoL: Professional Quality of Life Scale.

^i^ARTIC: attitudes toward trauma-informed care.

^j^PCQ-S: Patient-Centered Climate Scale for staff.

^k^OUD: opioid use disorder.

^l^PCC: person-centered competence.

For the 20-month trial, there will be 8 surveys from baseline assessment at enrollment through the remaining 7 assessments conducted every 77 days. Survey responses will be collected using the Qualtrics platform, accessible directly by participants.

For all enrolled patients, a review of their methadone clinic medical chart will include the duration of their treatment at the clinic, from treatment initiation to discharge or study end, whichever occurs first. This review will take place at the conclusion of the study period in accordance with the data sharing agreement (DSA) established between the clinic organization and the University of Arizona. A feasibility test with a sample of 50 charts with deidentified data was conducted in June 2024 and confirmed timely data transfer, data completeness, and utility for outcome measurement for the pilot clinics. Our national survey of OTP clinic directors found that 22.2% of clinics allowed DSAs with researchers, but the vast majority (77.3%) indicated that such agreements were not allowed or that they were not aware of the clinic organization’s position on them [60]. For the purposes of the trial, then, only clinics allowing DSAs will be eligible for study enrollment. The following medical chart segments will be requested for each patient participant: (1) the digest of the patient history of starting and leaving treatment at that clinic (dates), (2) case notes, (3) discharge summary, (4) treatment plans, (5) milligram dosing, and (6) take-home medication status over time. Case notes include qualitative data on patient stability, challenges reported by the patient (eg, housing, transportation, safety, and dosing sufficiency), and instances of missed doses. For the trial, the data will be transferred using unique identifiers that will correspond with the study unique identifiers. No personally identifying information (name and street address) will be transferred.

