### Statistical Analysis

Our primary outcome is patient time to first treatment interruption (confirmed in the pilot). Secondary outcomes include treatment retention (yes or no) at selected time points (1, 3, 6, and 12 months) and time to treatment discontinuation. To accommodate the clustering induced by nesting patients within clinics, we will use a mixed effects Cox proportional hazards model (shared frailty model) [61,62] to accommodate differential survival probability among clusters. The mixed model will include a random intercept for the clinic and a fixed treatment effect for MPACT or control assignment. We will also include patient-level covariates for age, sex, and time in MMT.

Our initial sample size calculation uses asymptotic normal results for log hazard ratio as well as sample size inflation factors (eg, Donner) [62] for cluster randomized trials. In designing the future R33 trial, we will make use of specific sample size methods for cluster randomized trials with time-to-event outcomes [63,64]. The relative frequency of first treatment interruption [65] is estimated as 66% at 12 months of MMT until we have confirmation from the pilot. We evaluate the number of clinics and number of patients, assuming that MPACT intervention reduces this frequency to 45% (n=240), 50% (n=300), and 55% (n=330). The power curves based on independent observations (no cluster effect) are shown in Figure 3. The graph shows that the recruitment of 30 clinics, with 20 patients per clinic, provides greater than 80% power to detect a difference in treatment interruption rates of 66% (control) and 55% (MPACT) with α=.05. Consistent with the cluster randomization trial design, we also consider the average number of patients per clinic as 10, 20, and 40 and different degrees of intraclinic clustering using intraclass correlation coefficients of 0.05 and 0.10.

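### Active in treatment is scored from a dose on single study days with no window, so a patient still in treatment who misses that one day counts as not retained

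*Protocol article*

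**What the plan says.** The Measures section of the protocol article measures retention in three ways:

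1. "time to first treatment interruption, calculated as the number of days to first missed dose from day 0 (MPACT enrollment".
2. Being active in treatment, "a binary (yes or no) if receiving dose at points in time on day 0, 30, 60, 90, and 120".
3. "continuous days in treatment during the study period, calculated as time (days) to discharge".

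The abstract repeats the second item among the measures of the primary study outcome, as "2) active in treatment at enrollment, day 30, 60, 90, and 120", and does not limit it to the pilot. Measures also states that what is collected in the pilot will be collected in the trial.

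The Statistical Analysis section names time to first interruption as the trial's primary outcome. It lists "treatment retention (yes or no) at selected time points (1, 3, 6, and 12 months" as a secondary outcome and does not say how yes or no is decided.

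The only tolerance around an assessment day is in Data Collection, "a completion forgiveness period of 5 days (day 35". It applies to completing a survey, not to dosing status. The chart elements requested in the same section include "5) milligram dosing, and (6) take-home medication status over time". The Introduction says that "MPACT promotes treatment flexibilities allowed by federal regulators".

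**The concern.** Retention means that the patient is still in treatment. A rule tied to one calendar day measures whether a dose was received on that day. The two differ for a patient who misses only that day. They may also differ where no dose is recorded because the clinic was closed or the patient was using take-home supply, if such days are not counted.

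The rule also sits badly beside its neighbours. Single missed doses are already captured by the first measure, and leaving treatment by the third. A patient without a dose on day 30 who is never discharged is not active on the second measure and continuously in treatment on the third.

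At stake is a retention outcome of the randomised trial. Random misses pull the two arms together. Misses linked to how doses are supplied could differ between arms, because the intervention encourages flexible delivery.

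**Working it through.** **The passages side by side.** The days 0, 30, 60, 90 and 120 fit the pilot's five 30-day assessments, and the pilot had a single arm. The trial's time points are 1, 3, 6 and 12 months. Days 30 and 90 correspond to 1 and 3 months. Six and 12 months have no counterpart in Measures, and days 60 and 120 have none in Statistical Analysis. The scoring rule reaches the trial through the abstract and the carry-over statement, and no other rule for a yes/no retention outcome is given.

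**No figure to reproduce.** The article gives no rate, sample size or power for this binary. Its power statement (66% against 55%) concerns treatment interruption. All rates below are assumptions chosen to show the range.

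**Formula.** Let q be the chance that a patient still in treatment has no recorded dose on the assessment day. Then apparent retention = true retention × (1 − q).

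**(a) How often a retained patient is scored no.** With four follow-up days and independent misses, the chance of at least one false no is 1 − (1 − q)^4.

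| q | At least one false no |
|---|---|
| 1/30 | 12.7% |
| 5% | 18.5% |
| 10% | 34.4% |

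**(b) Equal error in both arms.** The true difference is multiplied by (1 − q). Take true retention of 60% (control) and 70% (MPACT):

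- q = 5%: 0.60 × 0.95 = 57.0% and 0.70 × 0.95 = 66.5%, a difference of 9.5 points.
- q = 10%: 0.60 × 0.90 = 54.0% and 0.70 × 0.90 = 63.0%, a difference of 9.0 points.

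If true retention is equal at 70%, both arms appear as 63.0% at q = 10%, so no false difference arises.

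**(c) Unequal error, take-home days not counted.** Suppose q = 5% in control and 15% in MPACT.

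- Equal true retention of 70%: 0.70 × 0.95 = 66.5% against 0.70 × 0.85 = 59.5%, a false −7.0 points for MPACT.
- True 60% against 70%: 57.0% against 59.5%, so +10 points appears as +2.5.

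**(d) Unequal error, take-home days counted.** Suppose MPACT patients then miss fewer days, with q = 10% in control and 5% in MPACT.

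- Equal true retention of 70%: 63.0% against 66.5%, a false +3.5 points for MPACT.
- True 60% against 70%: 54.0% against 66.5%, so +10 points appears as +12.5.

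Cases (c) and (d) have opposite signs. What separates them is a counting rule that the article does not state, together with miss rates that it does not report.

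**The case against.** The strongest reply is that the article never says a dose must be observed in clinic. In ordinary words, a patient who takes a take-home dose on day 30 is receiving a dose. The outcome draws on surveys as well as charts, and take-home status is requested. Counting only clinic doses would also give every patient with take-home supply a missed dose on the first day at home, which would empty the first measure of meaning. This stands: scoring take-home patients as not retained is one possible reading, not the stated rule.

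A reader might go further and infer that the rule penalises the MPACT arm. For example, a patient attending weekly is away on 6 of 7 days. With 80% truly active in both arms, and 20% of control against 30% of MPACT patients attending weekly, apparent retention is 0.80 × (1 − 0.20 × 6/7) = 66.3% against 0.80 × (1 − 0.30 × 6/7) = 59.4%. The documents do not support that inference. It needs take-home days not to count and MPACT to raise their use, every rate is assumed, and case (d) shows that the bias can reverse.

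It is also fair to say that the day 0 to 120 schedule fits the pilot, which is complete and had no comparator, and that the binary is secondary in the trial.

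Finally, assessment windows are often left to the full protocol or SAP, which are not shown. That answers a complaint about missing detail. It does not answer this point, because the article states a rule (a dose on named single days), and that rule disagrees with the discharge-based measure beside it.

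**Conclusion.** The point holds as a measurement weakness in a trial secondary outcome. Read as written, the single-day rule scores some patients who are still in treatment as not retained, and it conflicts with time to discharge in the same list. It is the only rule the article offers for the trial's yes/no retention outcome.

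If misses are equally common in both arms, the loss is modest: a true 10-point difference becomes 9.5 points at an assumed 5% miss rate and 9.0 at 10%. A difference in error between arms is possible, but its direction and size are unknown and rest on how take-home days are counted. The 30-clinic, 600-patient sample size rests on time to first interruption and is not affected. This is a cheap improvement worth making before the trial starts, not evidence of a biased trial.

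**What to change.** For the trial, define active at each time point as at least one dose taken in clinic, or covered by dispensed take-home supply, within a fixed window around that day (for example 7 days either side). Derive it from the chart dosing and take-home records, and apply the same rule in both arms. A closed-clinic day or a single missed day then no longer decides the outcome.

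State which time points apply in the trial, so that Measures and Statistical Analysis agree. Say how the binary relates to time to discharge, in particular how a patient is scored who is not discharged but has no dose in the window.

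The cost is a sentence or two in the outcome definition, using chart elements already requested. The drawback is that a departure within the window is detected late: with 7 days either side, a patient who left up to 7 days before the time point still counts as active.

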### Data Collection

Primary and secondary study outcomes will be measured by surveys and patient chart reviews. Surveys will be administered monthly for the pilot study: assessment 1 (baseline at enrollment) and assessment 2-5 in 30-day sequences through the study period, with a contact reminder at day 27 and a completion forgiveness period of 5 days (day 35). Table 1 displays the sequencing of measures across the 5 pilot surveys.

**Table 1 table1:** Sequencing of Methadone Patient Access to Collaborative Treatment (MPACT) primary and secondary measures (assessment 1-5).

Construct		Assessment 1 (enrollment)			Assessment 2		Assessment 3		Assessment 4		Assessment 5 (study conclusion)
		Staff items, n	Patient items, n								
**Personal characteristics**											
	Demographics	5	6	—^a^		—		—		—	
	Personal SUD^b^ experience	10	—	—		—		—		—	
**Methadone treatment**											
	Time in MMT^c^ and clinic, reasons for choosing methadone as treatment	—	13	—		—		—		—	
	Methadone interruption	—	2	✓		✓		✓		✓	
	Dose, sufficiency, OD^d^	—	13	✓		✓		✓		✓	
**Trauma history and symptoms**											
	Trauma history (LEC^e^)	17	17	—		—		—		—	
	Vicarious Trauma Scale	8	—			✓				✓	
	PCL-5^f^ (trauma symptoms)	8	8	✓^g^		✓		✓^g^		✓	
**Burnout, compassion fatigue**											
	Burnout scale	9	—	✓		✓		✓		✓	
	ProQoL^h^ (compassion fatigue, Compass Sat, burnout)	9	—	✓		✓		✓		✓	
**Work characteristics**											
	Years working (SUD and this clinic) and role	5	—	—		—		—		—	
	Training and education for role	2	—	—		—		—		—	
**Baseline exposure to MPACT-related practices**											
	Reflect Sup (some staff)	1	—	✓		✓		✓		✓	
	Self-care	9	—	—		✓		—		✓	
	MPACT-specific practices	9	—	✓		✓		✓		✓	
**Empowerment**											
	Staff empowerment scale	5	—	—		✓		—		✓	
	Patient empowerment (Bann scale)	—	15	✓		✓		✓		✓	
**Beliefs**											
	Abstinence Orientation Scale	11	—	—		✓		—		✓	
	Comfort with MMT innovations	10	—	—		✓		—		✓	
	ARTIC^i^	10	—	—		✓		—		✓	
	Person-centered climate (PCQ-S^j^)	5	—	—		✓		—		✓	
**Stigma**											
	Stigma toward people with OUD^k^	8	—	—		✓		—		✓	
	Self-stigma	9	—	—		✓		—		✓	
	Fear of enacted stigma	9	—	—		✓		—		✓	
**Patient-centered care practices**											
	PCC^l^	19	—	—		✓		—		✓	
	Team-derived PCC scale	6	6	✓		✓		✓		✓	
	Kim Alliance Scale	—	16	✓		✓		✓		✓	
**Implementation**											
	MPACT feasibility, accept and fit; likelihood of continuing practices	5	—	—		—		—		✓	

^a^Not applicable.

^b^SUD: substance use disorder.

^c^MMT: methadone maintenance treatment.

^d^OD: opioid overdose.

^e^LEC: Life Events Checklist.

^f^PCL-5: Posttraumatic Stress Disorder Checklist.

^g^Patients only.

^h^ProQoL: Professional Quality of Life Scale.

^i^ARTIC: attitudes toward trauma-informed care.

^j^PCQ-S: Patient-Centered Climate Scale for staff.

^k^OUD: opioid use disorder.

^l^PCC: person-centered competence.

For the 20-month trial, there will be 8 surveys from baseline assessment at enrollment through the remaining 7 assessments conducted every 77 days. Survey responses will be collected using the Qualtrics platform, accessible directly by participants.

For all enrolled patients, a review of their methadone clinic medical chart will include the duration of their treatment at the clinic, from treatment initiation to discharge or study end, whichever occurs first. This review will take place at the conclusion of the study period in accordance with the data sharing agreement (DSA) established between the clinic organization and the University of Arizona. A feasibility test with a sample of 50 charts with deidentified data was conducted in June 2024 and confirmed timely data transfer, data completeness, and utility for outcome measurement for the pilot clinics. Our national survey of OTP clinic directors found that 22.2% of clinics allowed DSAs with researchers, but the vast majority (77.3%) indicated that such agreements were not allowed or that they were not aware of the clinic organization’s position on them [60]. For the purposes of the trial, then, only clinics allowing DSAs will be eligible for study enrollment. The following medical chart segments will be requested for each patient participant: (1) the digest of the patient history of starting and leaving treatment at that clinic (dates), (2) case notes, (3) discharge summary, (4) treatment plans, (5) milligram dosing, and (6) take-home medication status over time. Case notes include qualitative data on patient stability, challenges reported by the patient (eg, housing, transportation, safety, and dosing sufficiency), and instances of missed doses. For the trial, the data will be transferred using unique identifiers that will correspond with the study unique identifiers. No personally identifying information (name and street address) will be transferred.

### Study Recruitment

Recruitment is stepwise for both the pilot and the trial. For the national trial, clinics will first be recruited through email from a national list of methadone clinics responding to a prior survey by this team during 2024 [60]. A second strategy will involve an email to the state opioid treatment authority with a request to forward study information and the recruitment flyer to methadone clinic directors in their state. State opioid treatment authorities are the single opioid regulator in each state. Clinics that allow study recruitment among staff and patients, establish a DSA for the transfer of patient participant methadone treatment chart data at the conclusion of the 20-month trial, and identify a clinic “champion” to assist with study enrollment and study contact will be eligible for randomization as described below.

Following clinic enrollment, each clinic champion will post recruitment flyers in staff-only areas (for staff participants) and in patient-only areas (for patient participants). Recruitment flyers for staff lead to a study portal (web-based) presenting information about the study and requesting agreement to participate. If agreement is made, staff participants will immediately complete the enrollment survey (baseline assessment 1). The same process will occur for patients. Payment for timely completion of each survey is US $20 for patients and staff. This cost was determined by a group of staff and patients who completed the work associated with aim 1.

Patient and staff confidentiality will be maintained by centralizing the enrollment process. Recruitment flyers will be displayed in staff-only and patient-only areas with a QR code or URL leading to information for potential participants to learn more about the study and to voluntarily enroll. This process ensures the anonymity of study participants within the clinic, meaning that patients and staff participants will not be known to the study clinic. Further, at the time of enrollment, a unique identifier will be established by the participant and will be used henceforth. At no time will the clinic leadership or clinic champion know the identity of the study participants. The only exception to this is at the conclusion of the study when patient chart data transfer will occur, and at that time, only 1 person handling data transfer will have the name and dates of birth of the participants whose charts will be transferred for study purposes.

